#### Secondary outcomes

Secondary outcomes include the average change in office systolic and diastolic blood pressure as well as cardiorespiratory fitness, muscular strength and power and quality of life evaluated at baseline and after 12-week intervention in both arms. Additional measures of office blood pressure and enjoyment level during beach tennis sessions will be assessed at weeks 1, 4, 5, 8, 9 and 12.

### Participant timeline and data collection

Participants will be recruited from electronic medical records, phone calls, e-flyers in social media, word of mouth, and personal references. Patients potentially eligible for the study will be contacted by telephone by the trial investigator, who will explain the study and ascertain the patient’s interest to participate. Those who accept to participate will attend the Center for Clinical Research of Hospital de Clínicas de Porto Alegre, where the study consultations will be performed, to sign a consent form. The schedule of enrollment, interventions, and assessments is presented in Table 1. The allocation of participants and timeline are described below and presented in Fig. 1.

**Table 1 Tab1:**
[figure not shown]
Schedule of enrollment, interventions, and assessments from SPIRIT guidelines

**Fig. 1 Fig1:**
[figure not shown]
Recruitment and randomized allocation group from the CONSORT 2010 flow diagram

Those who signed the consent will undergo a clinical screening, resting electrocardiogram, anamnesis with sociodemographic, anthropometric and clinic data assessment, and questionnaire to evaluate quality of life. After that, the participants will perform a familiarization with strength and power muscle tests and with the mask that will be used in the cardiopulmonary test. In the second visit, participants will place the equipment of ambulatory blood pressure monitoring. On the day after, each participant will return at the laboratory to remove the equipment and perform evaluations of the cardiorespiratory fitness, muscular strength and power. All variables are assessed at baseline and at study completion. Participants will be asked to maintain their habitual activity and dietary habits at the time of recruitment.

### Measurement of primary outcome

*Ambulatory blood pressure* will be assessed throughout 24 h in intervals of 15-min in daytime and 20-min in nighttime periods. Daytime period starts at 7 AM and night-time starts at 11 PM. Participants will receive a formulary to note day activities, symptoms, sleep time and wake-up time. Each exam is considered valid when at least 14 measurements during the day and seven measurements at night [28]. If any exam is not considered valid, a new exam will be conduct up to 48 h between them. The participants will be instructed to avoid physical exercises and alcohol ingestion 24 h prior to exam. Ambulatory blood pressure will be assessed using an automatic oscillometric device (ABP 2400, Mortara, Milwaukee, EUA).

### Measurement of secondary outcomes

*Office blood pressure* will be measured after 10–20 min of rest, with the participant sitting quietly in a chair, according to standardized guidelines [29]. Three measurements, 1–2 min apart, are performed in the arm with the highest initial value. The average of the two measurements is considered. Furthermore, post-exercise hypotension will be measured during intervention period throughout the first session of weeks 1, 4, 5, 8, 9 and 12. In these sessions, blood pressure will be assessed at the beginning of session (after 10–20 min rest) and at the end of session in intervals of 15-min, during 60-min. The measures will be taken using a validated automatic oscillometric device (HBP-1100, OMRON Healthcare). The participants should avoid caffeine, exercise and smoking for 24 h before the measurements.

*Cardiorespiratory fitness* will be assessed using an incremental exercise test on a treadmill in order to determine peak oxygen consumption. The protocol will consist of an initial velocity of 3.5 km/h with 1% inclination for the first 2 min. Thereafter, velocity and grade will be incremented by 0.4–0.6 km/h and 0.5–1.0% inclination, respectively, every 1 min until the participants achieve their volitional exhaustion [30]. The expired gas will be analyzed using a metabolic cart (Metalyzer 3B Cortex, Leipzig, Germany). Blood pressure, electrocardiogram and heart rate will be continuously monitored and recorded throughout the test. The incremental exercise test will be conducted under the direct supervision of a licensed physician.

#### Muscular strength and power

*Countermovement jump test* will be assessed using My Jump2 software for mobile [31]. The participant will perform a warm up consisted of 10 squat strength exercise plus 3–5 jumps with 2-min interval. For the correct execution of the test, participant will be instructed to maintain orthostatic position keep their hands on their waist throughout the test, to perform the transition phase between the squat and flight phase quickly, to jump as fast as possible and to land at the same starting point. Three attempts will be performed with 30-s rest interval.

*Medicine ball throwing test* will be assessed using a medicine ball of 1 kg for women and 2 kg for men. Each participant will remain seated at the floor in an upright standing posture, with 90° abduction shoulder position, arms shoulder-aligned and flexed elbows. We will instruct to throw the ball as fast as possible, performing full-speed movement. Three attempts will be performed with a 1-min rest interval.

*Chair-stand test* will be conducted using a folding chair without arms, with a seat height of 43.2 cm. The test will begin with the participant seated in the middle of the chair, back straight, feet approximately shoulder-width apart and placed on the floor at an angle slightly back from the knees. Arms should be crossed at the wrists and held against the chest. At the signal “go”, the participant will stand up (body erect and straight) and then return to the initial seated position. The total number of stands executed correctly within 30-s and time to perform the first five repetitions will be used during the analyses [32].

*Isometric handgrip strength* will be measured in both arms with an analogic hand dynamometer (Jamar Sammons Preston Rolyan, Bolingbrook, IL, USA). The participant will remain seated with upright posture, placing the forearm parallel to the ground (elbow flexed at 90°). Thereafter, the participants will be instructed to perform a maximal squeezing contraction with sustained (isometric) effort lasting 5-s. Three attempts will be performed in each hand with 30-s rest intervals.

*Quality of life* will be evaluated through WHOQOL-BREF questionnaire [33]. The questionnaire contains 26 questions and is divided into four different domains (physical, psychological, social and environmental). The participant alone will answer the questionnaire and researchers provide help only if requested.

*Enjoyment* can define the level of fun in the different interventions and we will assess this variable through the Physical Activity Enjoyment Scale (PACES). The scale is composed of 18 items in a bipolar affirmations format (i.e., “amused” versus “not-amused”) punctuated in a range from the minimum value “1” to the maximum value “7” [34].

### Data management

Data will be collected on standardized paper forms identified by participant number and trial ID and containing instructions for standardized operational procedures. From these forms, we will proceed with double data entry for primary, secondary, and additional outcomes. All data will be stored and managed using the Research Electronic Data Capture (REDCap), an electronic data capture tool hosted at the Hospital de Clínicas de Porto Alegre.

### Sample size and power calculation

Sample size for the primary outcome was calculated using estimates of effect sizes from randomized clinical trial with similar design [14]. This estimation was set a priori based on a behavioral intervention for middle-aged patients with hypertension and analyzed in an intention-to-treat approach. A sample size of 42 individuals with hypertension on 2:1 ratio (BTT, *n*= 28) and (Con, *n*=14) allowing a dropout rate of 10%, will be able to detect a difference of 4 ± 6 mmHg in systolic 24 h blood pressure between groups. Statistical power was set at 90% including a type I error rate of 5%. WinPepi software calculator was used to estimate the sample size [35].

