## Abstract

**Background:**

Different physical activities are widely recommended as non-pharmacological therapies to reduce blood pressure. However, the effectiveness of exercise programs is associated with its continuity and regularity, and the long-term adherence to traditional exercise interventions is often low. Recreational sports emerge as an alternative, being more captivating and able to retain individuals for longer periods. Besides, sport interventions have demonstrated improvements in physical fitness components that are associated with a lower incidence of hypertension. However, no studies have investigated the effects of recreational sports on 24 h ambulatory blood pressure. The aim of the present study is to evaluate the effect of beach tennis training on ambulatory blood pressure and physical fitness in individuals with hypertension.

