## Background

Hypertension is considered the most important modifiable risk factor for cardiovascular disease [1, 2] affecting nearly one-third of adults in Brazil [3] and worldwide [4] with increased prevalence throughout lifespan [5]. Although the usual treatment of hypertension is based on blood pressure lowering drugs, changes in lifestyle through physical exercise has emerged as an effective strategy for prevention and treatment of this condition [6]. A number of studies have shown that aerobic, resistance and combined training can reduce 24 h ambulatory blood pressure in hypertensive participants [7, 8].

The effectiveness of physical exercise programs seems to be directly associated with its continuity and regularity, and the long-term adherence to traditional exercise interventions (i.e., resistance and aerobic training) is often low [9]. One of the problems raised by individuals who do not adhere to exercise is the monotony and smaller motivation that those activities provide to their practitioners [10]. In this regard, recreational sports emerge as an alternative, being more captivating and able to retain individuals for longer periods and to sustain prolonged benefits to its practitioners [11, 12]. Promising results have been described with the use of recreational team sports on cardiovascular parameters [10, 13], including reduced BP in the office among participants with hypertension [14]. Although office blood pressure can be used to assess and diagnose hypertension, data assessing blood pressure through ambulatory blood pressure monitoring can provide additional information related to the benefits of recreational sports on blood pressure management, and future studies should investigate the effects of recreational sports on 24 h blood pressure.

The age-related decline in physical fitness components (i.e., cardiorespiratory fitness, muscular strength and power, balance, among others) [15] and physical activity levels [16] are also associated with increased prevalence of cardiovascular diseases. Different recreational sports, especially soccer [17] and other contact team sports [18, 19], have been studied over the last 10 years, suggesting that different sports could be effective for improving physical fitness and could be important for reducing risk of hypertension [20, 21]. In this regard, other sports modalities that can be practiced by middle-aged and older adults should be investigated to provide more information on this topic.

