To the best of our knowledge, no studies have investigated the chronic effects of team sports on 24 h ambulatory blood pressure and have assessed the effects of a beach tennis intervention in cardiovascular profile and physical fitness. Based on that, we designed this parallel randomized controlled trial to evaluate the effect of beach tennis training on 24 h ambulatory blood pressure and different physical fitness parameters in individuals with hypertension. The difference between the intervention arms in mean change from baseline in 24 h, daytime and nighttime systolic and diastolic ambulatory blood pressure at 12-weeks is the primary outcome; secondary outcomes are the difference between mean change in office blood pressure as well as cardiorespiratory fitness, muscular strength and power. We anticipate that 12 weeks of beach tennis training will reduce blood pressure when compared to a non-exercising control group. Additionally, our recreational beach tennis intervention will improve all physical fitness components in comparison to the baseline values.

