#### Primary outcome

The primary outcome is the change from baseline in 24 h, daytime and nighttime systolic and diastolic blood pressure measured by ambulatory blood pressure monitoring at 12 weeks.

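### The planning figure of 4 ± 6 mmHg for 24 h systolic pressure is credited to a reference that the protocol otherwise cites only for office pressure, so its 24 h basis is unexplained

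*Protocol article*

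**What the plan says.** The sample size section of the protocol article names its source: "Sample size for the primary outcome was calculated using estimates of effect sizes from randomized clinical trial with similar design [14"]. It describes that source as a behavioural intervention in middle-aged patients with hypertension. It then says that 42 participants, 28 in beach tennis and 14 in control, "will be able to detect a difference of 4 ± 6 mmHg in systolic 24 h blood pressure between groups", with 90% power, 5% type I error and a 10% dropout allowance.

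Reference 14 is described in one other place, the Background, where it supports a statement about recreational team sports: "including reduced BP in the office among participants with hypertension [14"]. The next sentence there contrasts office with ambulatory measurement and calls for studies of recreational sports on 24 h pressure.

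On existing 24 h evidence, the Abstract says that "no studies have investigated the effects of recreational sports on 24 h ambulatory blood pressure". The Background, qualified as being to the authors' knowledge, says that "no studies have investigated the chronic effects of team sports on 24 h ambulatory blood pressure". The Discussion calls this trial the first of its kind.

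The two measurements have different roles in the trial. For ambulatory pressure: "The primary outcome is the change from baseline in 24 h, daytime and nighttime systolic and diastolic blood pressure measured by ambulatory blood pressure monitoring". For office pressure: "Secondary outcomes include the average change in office systolic and diastolic blood pressure".

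**The concern.** Two parts of the article do not fit together. If reference 14 is a recreational team-sport trial, as the Background implies, and no such trial has measured 24 h pressure, then reference 14 cannot have supplied a 24 h difference or SD. The sample size section nevertheless gives the planning figure for 24 h systolic pressure and describes no step from an office result to an ambulatory one.

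The section's claim about what the trial can detect on its primary endpoint rests on this figure. Office and ambulatory pressure are measured with different devices and schedules: three seated readings in the office, against readings every 15 to 20 minutes over 24 h. Neither the mean change nor its SD can be assumed to carry over. If the claim lacks a 24 h basis, readers cannot tell which ambulatory effects a null result would rule out.

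**Working it through.** **1. The passages side by side**

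| Place in the protocol article | What it says |
|---|---|
| Sample size and power calculation | Effect sizes come from reference 14; figure stated for 24 h systolic pressure |
| Background, second paragraph | Reference 14 cited for reduced office pressure, among recreational team sports |
| Abstract; Background (aims); Discussion | No recreational or team-sport study has yet measured 24 h ambulatory pressure |
| Primary outcome; Secondary outcomes | Ambulatory pressure is primary, office pressure secondary |

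These can be reconciled in four ways: (a) the figure is an office result used as a proxy; (b) it was adapted from reference 14 in a way not reported; (c) reference 14 is the wrong citation in the sample size section; (d) the statement that no 24 h data exist is wrong. The article does not say which.

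**2. The plan's own sample size**

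Inputs from the sample size section: difference 4 mmHg, ± 6 read as SD 6 mmHg, 2:1 allocation, 5% error (two-sided assumed), 90% power, 10% dropout.

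- Control group: (1 + 1/2) × (1.960 + 1.282)² × 6² / 4² = 1.5 × 10.51 × 2.25 = 35.5, so 36.
- Total: 36 + 72 = 108 evaluable; 108 / 0.9 = 120.

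The stated 42 is not reproduced. That is a separate arithmetic problem, and it would exist whichever endpoint the figure described.

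**3. What 42 participants can detect**

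The documents give no SD of change for 24 h systolic pressure, so a range on both sides of 6 mmHg is assumed. Method: two-sample t-test, two-sided 5%, noncentral t, standard error = SD × √(1/n₁ + 1/n₂).

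- 28 versus 14: √(1/28 + 1/14) = 0.327, 40 degrees of freedom. The difference detectable with 90% power is about 1.087 × SD.
- 25 versus 13 (28 × 0.9 = 25.2 and 14 × 0.9 = 12.6): √(1/25 + 1/13) = 0.342, 36 degrees of freedom. The difference is about 1.139 × SD.

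| Assumed SD of change (mmHg) | Detectable, 28 vs 14 | Detectable, 25 vs 13 | Power for 4 mmHg, 28 vs 14 | Power for 4 mmHg, 25 vs 13 |
|---|---|---|---|---|
| 4 | 4.3 | 4.6 | 85% | 81% |
| 5 | 5.4 | 5.7 | 66% | 62% |
| 6 | 6.5 | 6.8 | 51% | 48% |
| 8 | 8.7 | 9.1 | 32% | 30% |

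The SD 6 row shows the arithmetic shortfall from step 2. Only the spread between rows bears on the present point: it shows how far the detection claim depends on an SD for which no 24 h source is given.

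**The case against.** The article never calls reference 14 an office blood pressure study. It cites one result from it and does not say what else that trial measured. The reference is not at hand, so its endpoints cannot be checked. This objection stands. A reader might infer that an office value was simply relabelled as a 24 h value, but the documents do not establish that.

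The citation may be misnumbered. Reference 35 supports the sample size software in one section and injury risk in the Discussion, so the numbering is not dependable. The sample size section also describes its source as a behavioural intervention, not a sport. This stands as a live explanation, and the citation would then need correcting.

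The figure may be an adapted or target difference, since the text says only that effect sizes from reference 14 were used. That is possible, but no adaptation is reported.

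A reader might also infer that the true ambulatory effect must be smaller or its SD larger, so that the trial is weaker than planned. The documents do not support this. Ambulatory monitoring averages many readings, and a smaller SD is at least as plausible; at SD 3, power for 4 mmHg with 28 versus 14 would be 98%.

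Finally, the planned 95% confidence intervals would show the imprecision of a null result. That limits the harm but does not repair the stated detection claim.

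**Conclusion.** The concern holds as a conflict between the stated source and the stated endpoint. The article presents 4 ± 6 mmHg as a 24 h systolic figure resting on reference 14, while its other statements leave no room for a 24 h estimate there. Unless the citation is wrong or an unreported adaptation was made, the figure has no 24 h source.

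The direction of any error cannot be told from the documents. Over assumed SDs of 4 to 8 mmHg, the difference detectable with 90% power runs from 4.3 to 8.7 mmHg with all 42 participants, and from 4.6 to 9.1 mmHg after 10% dropout. This assumes a two-sided 5% t-test and that ± 6 denotes an SD. A baseline-adjusted analysis could do better if the correlation between baseline and follow-up is high, but the article states no such correlation.

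The power of about 51% (48% after dropout) at 4 mmHg and SD 6 belongs to the separate arithmetic error and must not be counted as the size of this mismatch. The point is worth correcting because the trial's stated ability to detect an effect on its primary endpoint depends on the figure.

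**What to change.** In the sample size section:

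- Correct the citation if reference 14 is not the source. If it is, label 4 ± 6 mmHg as an office-based proxy or a target difference, and state any adaptation.
- Take the SD of change, and a plausible difference, from 24 h ambulatory training data. The trials cited as references 7 and 8 in the Background are candidates. Say openly that they tested aerobic, resistance and combined training rather than a sport. The group's own beach tennis study covered the acute effects of a single session, so it cannot be assumed to supply an SD of 12-week change.
- Keep 42 participants, and replace the claim of 90% power for 4 mmHg with the detectable difference over an SD range on both sides of 6 mmHg, before and after dropout, as tabulated above.

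The cost is one reworded paragraph and a short recalculation, with no extra participants. The stated detectable difference will be larger than 4 mmHg at every SD tabulated.

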**Methods:**

This study will be a randomized, single-blinded, two-arm, parallel, and superiority trial. Forty-two participants aged 35–65 years with previous diagnosis of hypertension will be randomized to 12 weeks of beach tennis training group (two sessions per week lasting 45–60 min) or a non-exercising control group. Ambulatory (primary outcome) and office blood pressures, cardiorespiratory fitness, muscle strength/power and quality of life will be assessed at baseline and after the intervention period.

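### The stated 90% power does not follow from the sample-size inputs: 28 versus 14 participants give about 51% power for 4 mmHg with an SD of 6, and about 47% after 10% loss

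*Protocol article*

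**What the plan says.** The section on sample size and power calculation gives the size and allocation: "A sample size of 42 individuals with hypertension on 2:1 ratio (BTT, *n*= 28) and (Con, *n*=14) allowing a dropout rate of 10"%. It gives the target: the trial "will be able to detect a difference of 4 ± 6 mmHg in systolic 24 h blood pressure between groups". It then gives the operating characteristics: "Statistical power was set at 90% including a type I error rate of 5"%. The effect-size estimates are attributed to a cited randomised trial of similar design, and the software is named.

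The section does not label the ± 6. It gives no sidedness, no baseline to follow-up correlation and no other SD.

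Elsewhere, the abstract describes a two-arm parallel superiority trial of 42 participants. The Background section defines the primary comparison as "The difference between the intervention arms in mean change from baseline in 24 h, daytime and nighttime systolic and diastolic ambulatory blood pressure at 12-weeks". The statistical analysis section specifies GEE for correlated measures in all randomised participants, with 95% confidence intervals.

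**The concern.** The paragraph gives both the inputs and the result of a two-group calculation, so it can be checked directly. A difference of 4 against an SD of 6 is a standardised effect of 4/6 = 0.67. With only 14 in the smaller arm, 90% power for an effect of that size is implausible on its face.

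This paragraph is the only justification given for the size of the trial. If the power is near one half, the chance of missing a true 4 mmHg effect is also about one half, not the 10% that the text implies. A non-significant result set against a claimed 90% power would look like fair evidence that beach tennis training does not lower ambulatory pressure, and the design would not support that reading.

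**Working it through.** **Inputs, all from the sample-size section.** Difference δ = 4 mmHg; type I error 5%; n₁ = 28, n₂ = 14. With 10% lost, 42 × 0.9 = 37.8, so about 38 completers, taken as 25 and 13.

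**Assumptions.** SD σ = 6 mmHg for the analysed quantity, because the ± is unlabelled and the primary outcome is change from baseline. The test is two-sided, because no sidedness is given; one-sided is also tried.

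**Attempt to reproduce 90%.** Two-sample t-test, with SE = σ√(1/n₁ + 1/n₂), noncentrality λ = δ/SE and n₁ + n₂ − 2 degrees of freedom.

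- 28 vs 14: SE = 6 × √(1/28 + 1/14) = 6 × 0.327 = 1.964; λ = 4/1.964 = 2.037; 40 df; critical value 2.021. Power = **0.511**.
- 25 vs 13: SE = 6 × √(1/25 + 1/13) = 6 × 0.342 = 2.052; λ = 4/2.052 = 1.950; 36 df; critical value 2.028. Power = **0.475**. With the fractional sizes 25.2 and 12.6 it is 0.468.

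The stated 90% is not reproduced. Other readings of the same inputs do not reach it either:

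| Variant | 28 vs 14 | 25 vs 13 |
|---|---|---|
| Two-sided t-test | 0.511 | 0.475 |
| Two-sided, normal approximation | 0.531 | 0.496 |
| One-sided t-test | 0.640 | 0.606 |

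Equal allocation (21 vs 21) would give 0.559 two-sided and 0.684 one-sided.

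**What would give 90% at this size (two-sided t-test).**

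| Quantity | 28 vs 14 | 25 vs 13 |
|---|---|---|
| Difference for 90% power, SD 6 | 6.52 mmHg | 6.84 mmHg |
| Difference for 80% power, SD 6 | 5.64 mmHg | 5.91 mmHg |
| SD for 90% power, difference 4 | 3.68 mmHg | 3.51 mmHg |

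**What the stated inputs would require.** At 2:1, 72 + 36 gives power 0.899, just short, so 74 + 37 = 111 completers are needed. Then 111/0.9 = 123.3, which rounds up to 124 randomised.

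**If 6 is a single-time-point SD.** With correlation ρ between baseline and follow-up, the effective SD is 6√(1 − ρ²) under baseline adjustment and 6√(2(1 − ρ)) for a change score.

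- Baseline adjustment: solving 6√(1 − ρ²) = 3.68 gives ρ = √(1 − (3.68/6)²) = 0.79. For 3.51, ρ = 0.81.
- Change score: solving 6√(2(1 − ρ)) = 3.68 gives ρ = 1 − (3.68/6)²/2 = 0.81. For 3.51, ρ = 0.83.
- Baseline-adjusted power over a range of assumed correlations (28 vs 14, then 25 vs 13): 0.63 and 0.59 at ρ = 0.5; 0.79 and 0.76 at ρ = 0.7; 0.91 and 0.89 at ρ = 0.8.

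**The case against.** The strongest objection is that the ± 6 has no label. The planned model is for correlated measures, the estimates come from a cited trial that is not available here, and an article may condense a fuller calculation. If 6 is a single-time-point SD and a correlation of about 0.8 was assumed, baseline adjustment brings power to about 90%. This stands as a limit on the claim: the 47–51% is conditional on 6 being the SD of the analysed change. It does not rescue the text, which states no correlation. The primary outcome is a change from baseline, so the SD of change is the more natural reading, and on that reading the correlation is already contained in the 6.

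It can also be said that 47% is the pessimistic end, because the outcome section plans to assess drop-outs at 12 weeks and the analysis includes everyone randomised. That is fair, but full follow-up raises the figure only to 51%.

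A reader might go further and infer that the design could not exclude a 4 mmHg benefit. The documents do not support that. On the same inputs the 95% CI half-width is 2.021 × 1.964 = 3.97 mmHg (28 vs 14) or 2.028 × 2.052 = 4.16 mmHg (25 vs 13). An estimate of no effect with all 42, or one about 0.2 mmHg in the unfavourable direction with 38, would exclude it. Nor does the protocol say that a non-significant result will be read as no effect. The concern is that the stated power invites that reading.

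**Conclusion.** The point holds in conditional form. The 90% cannot be reproduced from the inputs printed beside it. With δ = 4 mmHg, 6 mmHg as the SD of change and a 5% type I error, power is about 51% with all 42 participants and about 47% if 10% are lost; one-sided it is 61–64%. The overstatement is therefore about 40 percentage points two-sided and over 25 one-sided. The choice between the t-test and the normal approximation moves the figures by only about two points.

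The result rests on two assumptions that the text leaves open: what the ± 6 denotes, and the sidedness. Of the readings examined, only a single-time-point SD with an unstated correlation of about 0.8 comes near 90%. It would be too strong to say that the true power is 51% on any reading. What the document supports is that the stated power does not follow from its stated inputs.

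**What to change.** Correct the sample-size paragraph in one of two ways.

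1. If 6 mmHg is the SD of change, keep 42 participants and state either that power for 4 mmHg is about 47–51%, or that the difference detectable with 90% power is about 6.5–6.8 mmHg (5.6–5.9 mmHg for 80%).
2. If another input was used (a different SD of change, a baseline to follow-up correlation, or a one-sided test), state it with its source and show that it reproduces 90% with 42 randomised and 10% lost.

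In either case, say whether the test is one- or two-sided and what the ± 6 is. Add a sentence that a non-significant primary result will be interpreted from the 95% confidence interval, which the statistical analysis section already plans, and not from a claimed 90% power.

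The cost is wording only, with no added participants, visits or procedures. Under the first option the stated power becomes less favourable. The figure of about 124 randomised is given for reference and is not a request to enlarge the trial.
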